### Follow-up

The clinical evaluation will be performed during follow-up at 40 weeks, 12 months, and 24 months of corrected age. Weight, height, and head circumference will be measured, and the child's complete structured physical evaluation will be performed at each visit. A comprehensive neurodevelopmental assessment using the Bayley IV scale will be served at a two-year follow-up.

### Unblinding

The blinding will be opened in those emergency cases in which knowledge of the assigned treatment is essential for the medical care and well-being of the patient. In such a case, the researcher should note the date and reason for unblinding.

The researcher or neonatologist in charge will contact the Blood Bank Service or unblinded operator, and the patient's treatment information will be provided. The blinding will be opened once the last patient enrolled in the study has been discharged from the hospital so that the results can be statistically analyzed. The neurodevelopmental specialist performing the long-term follow-up will remain blinded until the 24-month corrected age control of the last patient included in the study.

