## Abstract

**Background:**

Currently, the treatment of anemia in preterm infants is based on packed red blood cell (RBC) transfusions from adult donors. Oxygen (O2) is mainly transported to the tissues bound to hemoglobin (Hb). In extremely low gestational age neonates (ELGANs), fetal hemoglobin (HbF), which has a higher affinity for O2, represents up to 95% of circulating hemoglobin. During the first month of life, the majority of ELGANs will require an adult-donor RBC transfusion causing HbF levels to rapidly drop. HbA releases 50% more oxygen in peripheral tissues than HbF. Increased release of O2 in the retina is one of the main factors related to the development of retinopathy of prematurity (ROP). Collecting umbilical cord blood and using autologous umbilical cord whole blood (UCB) transfusions would contribute to maintaining physiological HbF concentrations in newborns and avoid oxygen-in-excess derived damage.

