Red blood cell (RBC) transfusions have been associated with a higher incidence of ROP, and its severity is directly related to the volume of blood transfused (11). In term newborns, fetal hemoglobin makes up about 60%–80% of total hemoglobin. In ELGANS, fetal hemoglobin makes up 90%–95% of total hemoglobin (12). Although the physio-pathological mechanism is unknown, it is postulated to be linked to the significant increase in adult hemoglobin (HbA) levels. HbA releases up to 50% more oxygen than fetal hemoglobin (HbF) to peripheral tissues. Because blood from bank donors comes exclusively from adults, RBC transfusions increase HbA levels generating a hyperoxic stimulus in the retinal capillaries that could trigger the development of ROP (13–15). Moreover, low HbF levels have also been associated with ROP (16, 17). Additionally, recent studies have suggested that HbF could protect against oxidative stress due to its biochemical properties (18, 19).

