### Intervention

Patients will be randomized to receive either whole UCBa, intervention group, or standard adult-donor packed RBC, control group. For patients with anemia requiring blood transfusion according to the Spanish Society of Neonatology's standards Committee threshold's recommendations (30), the responsible physician will make the corresponding request for transfusion indicating the volume needed. The Blook Bank will supply UCBa or RBC according to the patient's group, but bag labeling will be indistinguishable. In case there is not enough UCBa, RBC will be administered. As the maximum storage of UCB is 35 days, both groups will receive adult-donor RBC concentrates after this age. Transfusion's traceability will always be maintained through the e-Delphyn Transfusion Service software. UCB extraction and storage protocols are detailed in Appendix I.

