### Secondary outcomes

Outcomes related to effectiveness
-Recovery of hematocrit and hemoglobin values.-Transfusion requirements during admission (number and volume of transfusions received).-Treatment with EPO and other adjuvant treatments for anemia such as iron and folic acid supplementation (time of initiation, number of doses received).-Assessment of post-transfusion tissue oxygen transfer status: Brain and somatic NIRS value, oxygen saturation measured by pulse oximetry, lactate, HbF levels.Outcomes related to safety
-Incidence of acute transfusion reactions.-Incidence of late complications: bronchopulmonary dysplasia, periventricular leukomalacia, necrotizing enterocolitis, hemodynamically significant patent ductus arteriosus, sepsis, and death.Outcomes related to retinopathy markers
-Serum levels of EPO, VEGF and IGF-1.-HbF levels.Outcomes related to ROP treatment
-ROP severity-Laser therapy-Anti-VEGF administrationOutcomes related to UCB cellularity and oxidative stress.
-Quantification of reactive oxygen species in urine.-Composition of stem cells in UCB.

Data concerning retinopathy and oxidative stress biomarkers quantification and stem cells typification is provided in Appendix II.

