### Randomization and blinding

Randomization will be done just before birth and generated by random numbers using the R® 3.5.1 software (R Development Core Team, Auckland, New Zealand). Patient numbers will be assigned sequentially by order of entry into the study. Randomization will be stratified into two groups by gestational age (GA) (23–25 and 26–28), using block randomization. The Biostatistics Unit will provide a randomization list for the corresponding Neonatology Service containing the patient number and another for the Blood Bank Service holding the related treatment branch and the patient number. The neonatologist in charge of the patient will assign the patient a number for the study, ensuring that it has not been given to any other patient. Once the number has been provided, it will be sent to the Blood Bank, responsible for keeping the randomization list containing all the information about it.

The Blood Bank will receive the UCB from the delivery room. It will verify that it meets the quality criteria established by the Blood Bank and aliquot it into one or several units of blood, depending on the volume available. Once a transfusion is prescribed for a participating patient, the Blood Bank will dispense either UCB or RBC according to the assigned group in the same container bag typically used in the Neonatology Unit to be indistinguishable from guaranteeing the blinding. The neonatologist will remain blind to the randomization group, as will the nursing staff and specialists in charge of patient care.

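### The code opens when the last enrolled infant goes home, an event not tied to final ROP status for every infant

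*Protocol article*

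**What the plan says.** The Unblinding section of the protocol article sets one general rule: "The blinding will be opened once the last patient enrolled in the study has been discharged from the hospital". The stated purpose is to allow the statistical analysis. One person is excepted: the neurodevelopmental specialist stays blind until the last infant's 24-month visit.

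Under Randomization and blinding, "The neonatologist will remain blind to the randomization group, as will the nursing staff and specialists in charge of patient care". The masking described there and under Intervention is of the bag and its label.

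The Primary outcome section has ROP diagnosed and staged by an expert ophthalmologist, with no examination schedule or end date. ROP severity, laser therapy and anti-VEGF use are secondary outcomes. The sample size section takes death or ROP as the primary variable and describes ROP as appearing late after birth.

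The Secondary outcomes section also lists "Assessment of post-transfusion tissue oxygen transfer status: Brain and somatic NIRS value, oxygen saturation measured by pulse oximetry, lactate, HbF levels". The Abstract says that "the majority of ELGANs will require an adult-donor RBC transfusion causing HbF levels to rapidly drop", and the Introduction expects autologous cord blood to keep HbF high.

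**The concern.** A trial with an examiner-judged primary outcome needs allocation concealed until that outcome is final for everyone. The article ties code-breaking to a hospital event instead. Discharge says nothing about whether retinal examinations are finished. The event is also the discharge of one particular infant, the last to be enrolled, which need not be the last discharge in the trial.

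If the code opens while some infants are still being examined, ROP diagnosis, staging and the decision to treat could be made with the arm known. With 67 infants per arm, each infant whose ROP status was swayed would move that arm's incidence by 1/67 = 1.5 percentage points. The planned difference is 41% − 20.5% = 20.5 points.

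A second, weaker route to the allocation is HbF. It is an outcome measured after transfusion, and on the trial's rationale it should behave differently in the two arms.

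**Working it through.** The article gives no figure for this point, so the check compares its sections and adds three illustrations on stated assumptions.

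**1. Trigger against endpoint.** The trigger is discharge of the last enrolled infant. The endpoint is ROP, or death or ROP. No section makes final ROP status a condition of discharge or of unblinding. After the code opens, only the neurodevelopmental specialist is named as remaining blind. The ophthalmologist is presumably among the specialists covered by the general blinding statement, but that cover ends when the code opens.

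**2. Can an earlier-enrolled infant be less mature than the last one?** Gestational age at entry runs from 23 weeks (lower stratum limit) to 28+6 weeks (inclusion criterion).
- Spread: 28+6 − 23+0 = 5 weeks 6 days = 41 days.
- If the last enrolled infant is born at 28+6, and another was born at 23+0 on a date *d* days earlier, the earlier infant's postmenstrual age minus the last infant's is *d* − 41 days on any calendar date. For *d* below 41 the earlier-enrolled infant is the less mature one.
- Assuming even accrual of 134 infants over three years (1,095 days), the number enrolled in the final 41 days is 134 × 41/1,095 = 5.0, or 5.0/134 = 3.7%.

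On postmenstrual age alone this overstates the number affected, because not all of them will be born at 23 weeks and the last infant need not be born at 28+6. It does not count infants kept in hospital for other reasons, or infants sent home with examinations still due. The article gives nothing from which to estimate those.

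**3. Visits still open at unblinding.** Assume even accrual over 36 months and last discharge 2 to 4 months after the last birth, so unblinding falls at month 38 to 40. Deaths are ignored.
- Term is reached 17 weeks (3.9 months) after birth at 23+0, and 11 weeks 1 day (2.6 months) after birth at 28+6. The 24-month corrected visit therefore falls 26.6 to 27.9 months after birth.
- Still awaiting it: from (36 − (40 − 26.6))/36 = 63% to (36 − (38 − 27.9))/36 = 72%, or 84 to 96 of 134.

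**4. HbF as a marker of arm.** The Introduction states that "In ELGANS, fetal hemoglobin makes up 90%–95% of total hemoglobin". Assume a blood volume of 85 ml/kg and a haematocrit of 30%, giving 85 × 0.30 = 25.5 ml/kg of own red cells. Assume also that 5.5 to 13 ml/kg of adult red cells are given.

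HbF afterwards = baseline × 25.5/(25.5 + donor red cells)

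| Donor red cells (ml/kg) | Baseline 90% | Baseline 95% |
|---|---|---|
| 5.5 | 74.0% | 78.1% |
| 9 | 66.5% | 70.2% |
| 13 | 59.6% | 62.9% |

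Autologous blood would leave the percentage roughly unchanged. The Intervention section, however, says "In case there is not enough UCBa, RBC will be administered", and both arms receive adult blood once stored cord blood passes 35 days. The Discussion expects adult blood to be needed as a supplement in most cases. A low value can therefore occur in either arm. A value that stays high after a transfusion is informative and points to cord blood.

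**The case against.** Several points on the other side are sound.

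- **Open ROP status at the trigger is not demonstrated.** The article gives no examination window, and the full protocol may ensure that all ROP data are in. Since the code is opened in order to analyse results, the team may well intend that.
- **Few infants are at risk.** With recruitment spread over about three years, most infants will have had their ROP status settled under blind.
- **The long-term assessment is protected.** A reader might infer from "The clinical evaluation will be performed during follow-up at 40 weeks, 12 months, and 24 months of corrected age" that unblinding at discharge compromises follow-up, since most 24-month visits would still be open. The judgement-dependent part, the Bayley assessment, is expressly kept blind. What remains is growth and physical examination, which are not listed among the secondary outcomes.
- **HbF is not shown to reach blinded staff.** A reader might infer that it reveals the arm. No section says that the treating team or the ophthalmologist sees it, and an article may leave the routing of results to the full protocol. Crossover to adult blood makes a low value ambiguous.

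These points limit the size of the problem and the language that can be used. They do not change the fact that the article states a rule for opening the code, and that the rule names an event which does not guarantee a complete primary outcome.

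**Conclusion.** The unblinding trigger is fixed to the wrong event and should be changed. The finding rests on the rule as written and on an examiner-judged primary outcome. It holds whether the endpoint is ROP or death or ROP.

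The likely size is small. It affects infants near the end of recruitment, about 5 of 134 on the even-accrual illustration, and the true number cannot be derived from the article.

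HbF is a secondary risk only. A sustained high value after transfusion would suggest the cord-blood arm, if someone meant to be blind saw it.

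The documents do not support stronger readings: that the double blind is already lost, that one HbF value separates the arms, or that most secondary endpoints are biased. Many of those endpoints are in-hospital or laboratory measures, largely settled by the last discharge. The exceptions are late ROP severity and treatment.

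**What to change.** Reword the general rule in the Unblinding section so that the code is opened once final ROP status, or death, has been recorded for all enrolled infants and the primary-outcome database is locked. Keep the emergency provision and the exception for the neurodevelopmental specialist as they stand.

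As a secondary safeguard, add a sentence under Randomization and blinding that study HbF results are withheld from the treating team and the ROP examiner until unblinding. If the full protocol already provides for this, a cross-reference is enough.

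The first change costs wording and possibly a delay in unblinding, whose length cannot be stated without an ROP examination schedule. The second needs an arrangement for routing results at the three hospitals, if none exists. Neither affects the sample size or the treatments.

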### Data collection and study monitoring

A record must be completed for each patient included in the study. Data will be anonymized using a unique code for each participant. The critical document containing each patient's name related to the code number will be stored in each center's principal investigator's folder. Data will be kept in an institutional research location of the principal investigator, secured with a password or key for the period specified by legislation.

During the trial, periodic monitoring visits will be carried out by an external monitor independent from the research team to ensure that the protocol and good clinical practices are followed. The monitors can review the source documents to confirm that the data collected are accurate. The researcher and the institution guarantee the monitors direct access to the source documents and the relevant regulatory authorities for verification.

### Adverse events (AEs)

Considering the characteristics of the investigated product, adverse events related to transfusions are managed in compliance with the regulations specified by the National Transplant Organization. The initiation of the study has been reported to the National Transplant Organization.

### Statistical analysis

The following sets of analyses are planned: (1) All included patients, regardless of whether they were transfused or not; (2) All included patients who received transfusions, as per intention-to-treat (including intervention group patients who received adult donor blood transfusions due to unavailability of umbilical cord blood); (3) All included patients who received transfusions as per protocol (excluding intervention group patients who received adult donor blood transfusions). Secondary analyses will also examine the effect of the two treatment strategies on the described secondary variables. An interim analysis of the results will be conducted once half of the sample has been collected to assess the presence of any relevant safety or mortality outcomes. An external committee will be proposed to perform the calculations while maintaining blinding until evaluation.

Categorical variables are described with each category's numerical count (percentage). If the application assumptions are met, they are compared with Pearson's chi-square test, and if not, Fisher's exact test. Continuous variables are represented with Tuckey box plots. If the constant variables are standard (*p* > 0.05 in the Shapiro–Wilk test), they are described with the mean ± standard deviation. They are compared using Student's *t*-test, first testing the hypothesis of equality of variances using Levene's test. If abnormal, they are described with a median (p25, p75) and compared with the nonparametric Mann–Whitney *U*-test. Comparison between both groups of repeated measures over time is performed by a two-way analysis of variance (ANOVA) test, first testing Mauchly's sphericity hypothesis and rejecting it with *p* < 0.05. Survival times are expressed with their median [95% confidence interval (95% CI)], and between-group comparison is performed with the log-rank test. Throughout the study, a *p* < 0.05 is accepted as the limit of statistical significance. The magnitude of the effect is quantified with the risk difference (expressed as a percentage), and its precision is indicated with the 95% CI.

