### Sample size calculation and power

We consider the development of ROP a competitive outcome with mortality due to its late onset during postnatal development. The combined variable death or ROP was considered the primary study variable. The incidence of death or ROP in our center in ≤28 weeks is 41%. A 50% reduction in the incidence will be considered clinically significant, so considering a significance level of 0.05 and a power of 0.8, the calculated sample size is 122 patients. Assuming a drop ratio of 10%, 134 patients will be recruited for the study (67 in each group).

University and Polytechnic Hospital La Fe is a tertiary center with 6,000–6,500 births annually. In addition, two other recruiting centers, University Clinical Hospital of Santiago (2,000–2,200 births annually) and Maternal and Child University Hospital Complex of Las Palmas (4,500–4,800 births annually), are included in the study, so we estimate that the sample size could be accomplished in the three years of the study duration.

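### Three analysis sets share one 0.05 limit with none named primary; the intention-to-treat label sits on a transfused-only subset, and the per-protocol set excludes infants from one arm only

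*Protocol article*

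**What the plan says.** The Statistical analysis section of the protocol article lists three sets:

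- Set 1: "All included patients, regardless of whether they were transfused or not".
- Set 2: "All included patients who received transfusions, as per intention-to-treat". A parenthesis adds that intervention infants given adult blood because cord blood was unavailable stay in.
- Set 3: "All included patients who received transfusions as per protocol (excluding intervention group patients who received adult donor blood transfusions").

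None is called primary. The secondary analyses mentioned next concern secondary variables, not sets 2 and 3. For p values, one limit covers the whole study: "0.05 is accepted as the limit of statistical significance". Sidedness is not stated, but precision is given by a 95% CI, which suggests two-sided tests. The Discussion returns to the sets as a way to gauge the effect of incomplete cord-blood supply, and does not rank them.

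Under Randomization and blinding: "Randomization will be done just before birth". Treating staff are blind to the arm.

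The primary variable is stated in two ways. The Abstract and the Primary outcome section give ROP incidence. The Sample size section gives death or ROP, with a 41% incidence at one center in infants of 28 weeks or less, not restricted to transfused infants.

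**The concern.** Whether an infant is transfused is known only after randomization, so set 2 is not an intention-to-treat population in the usual sense. It leaves out randomized infants who never need blood and those who die before a first transfusion. A result reported from it under that label would be read as the full randomized comparison, which is set 1.

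With no primary set and one threshold for all, the text does not say which result decides the trial. If any of the three could carry the claim, the false-positive rate exceeds 5%.

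Set 3 adds a different problem. Its exclusion applies to the intervention arm only and is tied to how much blood an infant needed relative to the cord blood available. The Discussion expects allogeneic supplements to be usual, so many intervention infants could be removed. The Introduction reports that ROP severity rises with transfused volume, so those who remain may be at lower risk whatever product they received. They are then compared with all transfused controls. Read literally, the exclusion also catches intervention infants transfused after 35 days, when the Intervention section moves both arms to adult blood.

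**Working it through.** **The plan's own figure.** The Sample size section says "considering a significance level of 0.05 and a power of 0.8, the calculated sample size is 122 patients". With p1 = 0.41, p2 = 0.205 and mean p = 0.3075, the pooled formula per arm is

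n = [z_α √(2 × 0.3075 × 0.6925) + z_0.80 √(0.41 × 0.59 + 0.205 × 0.795)]² / 0.205².

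- One-sided 0.05 (z = 1.645): 61.6, so 62 per arm, 124 in total, close to 122.
- Two-sided 0.05 (z = 1.960): 78.4, so 79 per arm, 158 in total.

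Sidedness is a separate matter. It is noted here because the checks below use two-sided tests, in line with the 95% CI.

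**Inputs for the error rate.** From the documents: 67 per arm, 1:1 allocation, 41% overall risk, Pearson chi-square, limit 0.05. Not in the documents, so assumed: share transfused 70–80%; share of transfused intervention infants who remain in set 3, 30–50%; and the risk splits below. Each scenario is 200,000 simulated trials with no treatment effect.

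**Check A: exclusions unrelated to risk.** Risk if untransfused is set at 15%. Risk if transfused follows from the 41% overall:

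- 70% transfused: (0.41 − 0.30 × 0.15)/0.70 = 0.521
- 80% transfused: (0.41 − 0.20 × 0.15)/0.80 = 0.475

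| Transfused | Kept in set 3 | Set 1 | Set 2 | Set 3 | Set 1 or 2 | Any of three |
|---|---|---|---|---|---|---|
| 70% | 30% | 4.7% | 5.1% | 5.1% | 7.3% | 10.6% |
| 70% | 50% | 4.7% | 5.1% | 5.2% | 7.3% | 9.8% |
| 80% | 30% | 4.6% | 5.1% | 5.1% | 6.8% | 10.1% |
| 80% | 50% | 4.7% | 5.0% | 5.2% | 6.8% | 9.3% |

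Each set alone holds about 5%; the excess comes from having three of them. Three independent tests would give 1 − 0.95³ = 14.3%, which overstates it because the sets are nested.

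**Check B: exclusions related to risk.** Risk is set at 20% if untransfused and 35% if cord blood alone would suffice, the same in both arms. The average risk among the transfused is (0.41 − 0.30 × 0.20)/0.70 = 0.500 at 70% transfused and (0.41 − 0.20 × 0.20)/0.80 = 0.4625 at 80%. The risk in infants with higher need is then (average − kept × 0.35)/(1 − kept).

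| Transfused | Kept in set 3 | Risk, higher need | Set 3: intervention vs control | Set 2 rejects | Set 3 rejects |
|---|---|---|---|---|---|
| 70% | 30% | 56.4% | 35% vs 50% | 5.1% | 16.6% |
| 70% | 50% | 65.0% | 35% vs 50% | 5.2% | 22.4% |
| 80% | 30% | 51.1% | 35% vs 46.25% | 5.0% | 12.1% |
| 80% | 50% | 57.5% | 35% vs 46.25% | 5.1% | 15.8% |

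With no treatment effect, set 3 expects a difference of 11 to 15 percentage points in favour of cord blood, and nearly all its rejections point that way. Set 2 stays at about 5% because its entry rule is the same in both arms.

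**The case against.** The full randomized comparison is planned, and it is listed first. The label on set 2 can be read as analysis by allocated arm among the transfused, in contrast to the per-protocol set, and the parenthesis shows exactly who is in it. The Discussion gives the sets a sensitivity role, and the 41% used for sizing fits set 1. The 0.05 sentence is a general convention, and ranking could come in a fuller document. All of this is fair, and it means that no analysis is missing. It does not remove the label, the absence of a primary set or the single threshold, which this text itself states.

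Three stronger readings are tempting and are not supported:

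- **That set 2 is a biased comparison.** The arms differ only in the product dispensed once a transfusion is prescribed, and prescribers are blind. If blinding holds, entry to set 2 should not depend on arm, and set 2 keeps its nominal error in both checks.
- **That set 2 loses primary events through early deaths.** This holds only if death or ROP is primary, as in the Sample size section. If ROP alone is primary, as in the Abstract and Primary outcome sections, those deaths are not events in any set.
- **That the plan allows success on any one set, or will report set 2 in place of set 1.** The text says neither; it is silent on which set decides.

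**Conclusion.** The point holds as a wrong label, an undesignated primary set and a per-protocol set that should not carry a claim. If any set could support the conclusion, the false-positive rate is about 9–11% instead of 5% when set 3's exclusions are unrelated to risk. Sets 1 and 2 alone account for about 7%. If infants managed on cord blood alone are at lower risk, set 3 by itself rejects a true null in about 12–22% of trials. That makes the one-sided exclusion the larger hazard, ahead of the label. These sizes rest on assumed transfused shares, retained shares and risk splits that the documents do not supply. The direction of the set 3 problem rests on the document's own statements that supplements are usual and that ROP severity rises with transfused volume. The change should be made before unblinding.

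**What to change.** In the Statistical analysis section:

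1. Name set 1, all randomized infants analysed as allocated, the intention-to-treat set and the sole primary analysis at two-sided 0.05.
2. Relabel set 2 as transfused infants, as allocated.
3. Declare sets 2 and 3 supportive, with no efficacy claim resting on them if set 1 is not significant. Reporting them as estimates with 95% CIs would suit that role.
4. State that set 3 is not a randomized comparison, because its exclusion acts on the intervention arm only.

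This brings the error rate of the deciding test back to about 5% (simulated 4.6–4.7% for set 1 in Check A). It changes wording only and needs no extra infants or data. The cost is that untransfused infants dilute the set 1 estimate; set 2 still shows the contrast among those transfused.
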